
### Who will take informed consent? {26a}

Consent will be taken by members of the study team who have been delegated the responsibility of taking informed consent by the Principal Investigator. Informed consent will be obtained and documented prior to the participant undergoing study procedures. The informed consent document will comply with Good Clinical Practice (GCP) and local regulatory guidelines.

Informed consent will be obtained in Chinese. The investigator will retain the original of each participant’s signed consent document. The informed consent document used in this study, and any changes made during the study, will be prospectively approved by the Research Ethics Committee/Institutional Review Board (REC/IRB). Participants are free to withdraw at any time from the study without providing a reason.

### Additional consent provisions for collection and use of participant data and biological specimens {26b}

Participants will be noticed and signed the informed consent for collection and storage of clinical data and biological samples. No individual personal data from patients will be contained in collection and use of the biological specimens.

#### Public and patient involvement

There will be no public or patient involvement in the design of the protocol of our study.

## Interventions

### Explanation for the choice of comparators {6b}

Baricitinib has been approved for the treatment for active RA. There are already some reports of baricitinib used in some other autoimmune diseases, such as SLE [20], dermatomyositis [21], and polymyalgia rheumatica/giant cell arteritis [7]. In a double-blind, multi-center, randomized, placebo-controlled, 24-week phase 2 study, baricitinib 4 mg per day significantly improved the signs and symptoms of active SLE, especially arthritis or rash, and showed a safety profile consistent with previous studies in RA [20]. So, we choose the dosage of baricitinib 4 mg per day in this study.

We had already observed that baricitinib treatment for 6 months significantly improved the symptoms and the ESSDAI score of active pSS patients in a pilot study established at PUMCH (see “Discussion”). Based on the basic researches and clinical studies mentioned above, we thought that baricitinib might have therapeutic benefit in patients with active pSS. The conventional treatment of SS includes topical and systemic medications such as HCQ, oral glucocorticoids, and immunosuppressive agents. We choose HCQ and low dose of steroids as the background treatment in our study.

### Intervention description {11a}

Patients with active pSS (ESSDAI ≥ 5) under 12 weeks treatment of HCQ will be involved in the study. Patients will be randomized (2:1) to receive baricitinib 4 mg per day + HCQ 400 mg per day or HCQ 400 mg per day alone. Patients will come to visit at weeks 0, 4, 8, 12, 16, 20, and 24. Patients who have no ESSDAI response to HCQ treatment alone at week 12 will be switched to baricitinib + HCQ group and added on with baricitinib 4 mg per day until the end of the study (week 24). The final evaluation will be at week 24.

### Criteria for discontinuing or modifying allocated interventions {11b}

#### Temporary interruption of investigational product

In some circumstances, patients may need to temporarily interrupt treatment as a result of abnormal laboratory values that may have an unclear relationship to investigational product.

For the abnormal laboratory findings and clinical events (regardless of relatedness) listed in Table 1, specific guidance is provided for temporarily interrupting treatment and when treatment may be restarted. Retest frequency and timing of follow-up laboratory tests to monitor the abnormal finding is at the discretion of the investigator. Investigational product that was temporarily interrupted because of an adverse event or abnormal laboratory value not specifically covered in Table 1 may be restarted at the discretion of the investigator.

**Table 1 Tab1:** Temporary interruption due to some abnormal laboratory values

Laboratory measure	Action	Monitoring guidance
Absolute neutrophil count (ANC)	Treatment should be interrupted if ANC < 1 × 10^9^ cells/L and may be restarted once ANC return above this value	Before treatment initiation (see exclusion criteria too) and thereafter according to routine patient management
Absolute lymphocyte count (ALC)	Treatment should be interrupted if ALC < 0.5 × 10^9^ cells/L and may be restarted once ALC return above this value	
Hemoglobin (Hgb)	Treatment should be interrupted if Hgb < 8 g/dL and may be restarted once Hgb return above this value	
Hepatic transaminases	Treatment should be temporarily interrupted if drug-induced liver injury is suspected	

### Permanent discontinuation from investigational product

Investigational product must be permanently discontinued if the patient or the patient’s designee requests to discontinue investigational product.

Discontinuation of the investigational product for abnormal liver tests should be considered by the investigator when a patient meets 1 of the following conditions:ALT or AST > 8 × upper limit of normalALT or AST > 5 × upper limit of normal for more than 2 weeks after temporary interruption of investigational productALT or AST > 3 × upper limit of normal and total bilirubin level > 2 × upper limit of normalALT or AST > 3 × upper limit of normal with the appearance of fatigue, nausea, vomiting, right upper quadrant pain or tenderness, fever, rash, and/or eosinophilia (> 5%)

Investigational product should be permanently discontinued if any of the following laboratory abnormalities are observed:WBC < 1 × 10^9^ cells/LANC < 0.5 × 10^9^ cells/LALC < 0.2 × 10^9^ cells/LHgb < 6.5 g/dL

Temporary interruption rules must be followed where applicable. For laboratory values that meet permanent discontinuation thresholds, investigational product should be discontinued. However, if in the opinion of the investigator the laboratory abnormality is due to intercurrent illness such as cholelithiasis or another identified factor, laboratory tests may be repeated. Only when the laboratory value meets resumption thresholds (Table 1) following the resolution of the intercurrent illness or other identified factors may the investigator restart investigational product.

In addition, patients will be discontinued from investigational product in the following circumstances:PregnancyMalignancyDevelopment of a VTE (DVT/PE) during the study

#### HBV DNA monitoring

HBV DNA testing will be performed in enrolled patients who tested positive for HBcAb at screening. Patients who are HBcAb-positive and HBV DNA-negative (undetectable) at Visit 1 will require HBV DNA monitoring every 3 months and at the patient’s last visit, regardless of their hepatitis B surface antibody (HBsAb) status. If a result is obtained with a value above limit of quantitation at any time during the study, the patient will be permanently discontinued from investigational product and should be referred to a hepatology specialist immediately.

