Patients with cervical carcinoma in situ that has been resected with no evidence of recurrence or metastatic disease for at least 3 years may participate in the study.bPatients with basal cell or squamous epithelial skin cancers that have been completely resected with no evidence of recurrence for at least 3 years may participate in the study.Have a current or recent (< 4 weeks prior to randomization) clinically serious viral, bacterial, fungal, or parasitic infection or any other active or recent infection that in the opinion of the investigator, would pose an unacceptable risk to the patient if participating in the study.Have symptomatic herpes simplex at the time of randomization, a history of disseminated/complicated herpes zoster, or have had symptomatic herpes zoster infection within 12 weeks prior to randomization.Have a positive test for hepatitis B virus (HBV) defined as:aPositive for hepatitis B surface antigen (HBsAg), orbPositive for hepatitis B core antibody (HBcAb) and positive for hepatitis B virus deoxyribonucleic acid (HBV DNA). Note: Patients who are HBcAb-positive and HBV DNA-negative may be enrolled in the study but will require additional HBV DNA monitoring during the study.Have hepatitis C virus (HCV) infection (hepatitis C antibody-positive and HCV ribonucleic acid [RNA]-positive). Note: Patients who have documented anti-HCV treatment for a past HCV infection AND are HCV RNA-negative may be enrolled in the study.Have evidence of human immunodeficiency virus (HIV) infection and/or positive HIV antibodies.Have had household contact with a person with active tuberculosis (TB) and did not receive appropriate and documented prophylaxis for TB.Have evidence of active TB or latent TB.aHave evidence of active TB, defined in this study as the following: Positive purified protein derivative (PPD) test (≥ 5 mm induration between approximately 2 and 3 days after application, regardless of vaccination history), medical history, clinical features, and abnormal chest X-ray at screening. QuantiFERON®-TB Gold test or T-SPOT®.TB test (as available and if compliant with local TB guidelines) may be used instead of the PPD test. Patients are excluded from the study if the test is not negative and there is clinical evidence of active TB. Exception: patients with a history of active TB who have documented evidence of appropriate treatment, have no history of re-exposure since their treatment was completed, have no clinical features of active TB, and have a screening chest X-ray with no evidence of active TB may be enrolled if other entry criteria are met. Such patients would not be required to undergo the protocol-specific TB testing for PPD, QuantiFERON®-TB Gold test, or T-SPOT®.TB test but must have a chest X-ray at screening (i.e., chest imaging performed within the past 6 months will not be accepted).bHave evidence of untreated/inadequately or inappropriately treated latent TB, defined in this study as the following: Positive PPD test, no clinical features consistent with active TB, and a chest X-ray with no evidence of active TB at screening; or If the PPD test is positive and the patient has no medical history or chest X-ray findings consistent with active TB, the patient may have a QuantiFERON®-TB Gold test or T-SPOT®.TB test (as available and if compliant with local TB guidelines). If the test results are not negative, the patient will be considered to have latent TB (for purposes of this study); or QuantiFERON®-TB Gold test or T- SPOT®.TB test (as available and if compliant with local TB guidelines) may be used instead of the PPD test. If the test results are positive, the patient will be considered to have latent TB. If the test is not negative, the test may be repeated once within approximately 2 weeks of the initial value. If the repeat test results are again not negative, the patient will be considered to have latent TB (for purposes of this study). Exception: Patients who have evidence of latent TB may be enrolled if he or she completes at least 4 weeks of appropriate treatment prior to randomization and agrees to complete the remainder of treatment while in the trial. Exception: Patients with a history of latent TB who have documented evidence of appropriate treatment, have no history of re-exposure since their treatment was completed, have no clinical features of active TB, and have a screening chest X-ray with no evidence of active TB may be enrolled if other entry criteria met. Such patients would not be required to undergo the protocol-specific TB testing for PPD, QuantiFERON®-TB Gold test, or T-SPOT®.TB test but must have a chest X-ray at screening (i.e., chest imaging performed within the past 6 months will not be accepted).Have been exposed to a live vaccine within 12 weeks of randomization or are expected to need/receive a live vaccine during the study (except for herpes zoster vaccination).Are currently enrolled in or have discontinued within 4 weeks of screening from any other clinical trial involving an investigational product or nonapproved use of a drug or device or any other type of medical research judged not to be scientifically or medically compatible with this study.Participants with active renal or central nervous system disease or significant impairment of major organ function (lung, heart, liver, kidney) or any condition that, in the opinion of the Investigator, would jeopardize the participant’s safety following exposure to the study drug.Psychiatric illness or history of medical non-compliance that the study team feels will make the patient unlikely to complete the study.Known allergic reactions to baricitinib or its components.Are largely or wholly incapacitated permitting little or no self-care, such as being bedridden or confined to wheelchair.In the opinion of the investigator, are at an unacceptable risk for participating in the study.Have donated more than a single unit of blood within 4 weeks prior to screening or intend to donate blood during the study.Have a history of intravenous drug abuse, other illicit drug abuse, or chronic alcohol abuse within the 2 years prior to screening or are concurrently using, or expected to use during the study, illicit drugs (including marijuana).Are unable or unwilling to make themselves available for the duration of the study and/or are unwilling to follow study restrictions/procedures.

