### Participant timeline {13}

Table 2 shows the participant timeline. The window period of each visit is 2 weeks.

**Table 2 Tab2:** The participant timeline

	− 4 weeks (screening)	0 weeks (start medication)	4 weeks	8 weeks	12 weeks (switch checkpoint)	16 weeks	20 weeks	24 weeks (the end of study)
Visit	0	1	2	3	4	5	6	7
informed consent	√							
Medical history record	√							
Vital signs	√	√	√	√	√	√	√	√
Infection screening like hepatitis and TB	√							√
complete blood cell count	√	√	√	√	√	√	√	√
Renal and liver function test	√	√	√	√	√	√	√	√
Urine routine test	√	√	√	√	√	√	√	√
Acute phase reactants (ESR, CRP)	√	√			√			√
Autoantibodies (antinuclear antibody, anti-SSA, anti-SSB, et al.)	√							√
Immunological parameters (Ig, complement, RF)	√				√			√
Exocrine gland function	√				√			√
Labial salivary gland biopsy	√							√
PGA score	√	√			√			√
ESSDAI score	√	√			√			√
ESSPRI score	√	√			√			√
Adverse events	√	√	√	√	√	√	√	√
Concomitant medication	√	√	√	√	√	√	√	√

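### Three-monthly HBV DNA testing is not carried into Table 2 at week 12, and an HBcAb-positive control may start baricitinib before that result is known

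*Protocol article*

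**What the plan says.** Under Exclusion criteria, a patient is excluded if positive for "hepatitis B core antibody (HBcAb) and positive for hepatitis B virus deoxyribonucleic acid (HBV DNA"). HBcAb-positive patients without detectable HBV DNA "may be enrolled in the study but will require additional HBV DNA monitoring during the study".

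The section HBV DNA monitoring sets the interval. Patients who are DNA negative "at Visit 1 will require HBV DNA monitoring every 3 months", and are tested again at their last visit. It adds the stop rule: "If a result is obtained with a value above limit of quantitation at any time during the study, the patient will be permanently discontinued". The rule applies to the study drug and comes with referral to a hepatology specialist.

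Table 2, under Participant timeline {13}, has one hepatitis row, "Infection screening like hepatitis and TB". It is ticked at -4 weeks (Visit 0) and at 24 weeks (Visit 7). The column for Visit 4, headed "12 weeks (switch checkpoint"), has no tick in that row. The text above the table says: "The window period of each visit is 2 weeks".

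The switch is defined in Intervention description {11a}: "Patients who have no ESSDAI response to HCQ treatment alone at week 12 will be switched to baricitinib + HCQ group". Interim analyses {21b} repeats it. Neither section names an HBV DNA condition.

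**The concern.** For a control who switches, week 12 is the first dose of baricitinib. At entry, the protocol requires HBV DNA to be negative before an HBcAb-positive patient can take part. At the switch it does not ask for that result again, although its own monitoring rule makes a test due at about the same time. The stop rule is written for a drug the patient is already taking, so a result that arrives after the switch acts only once exposure has begun.

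The schedule does not help a site avoid this. The only hepatitis row is blank at the switch visit, and the monitoring text refers to Visit 1, which Table 2 numbers as week 0 with no hepatitis tick. What is at stake is the safety of HBcAb-positive controls whose HBV DNA has become detectable since screening. The trial has no data safety monitoring board and plans no interim safety analysis, so it depends on the visit schedule to catch such cases.

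**Working it through.** The plan gives no figure to reproduce. The check compares the text with the schedule and adds calendar arithmetic.

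**1. When the first three-monthly test is due.** Three months = 365.25 / 4 / 7 = 13.0 weeks.
- Counted from Visit 1 (week 0): 0 + 13 = week 13.
- Counted from screening (week -4): -4 + 13 = week 9.

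**2. Which visit that is.** The visit window can be read in two ways.
- Plus or minus 2 weeks: Visit 4 spans 12 - 2 = week 10 to 12 + 2 = week 14.
- Two weeks in all: 12 - 1 = week 11 to 12 + 1 = week 13.

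Counted from week 0, the due date of week 13 lies inside Visit 4 on either reading. With visits at weeks 0, 4, 8, 12, 16, 20 and 24, Visit 4 is the natural three-month visit.

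**3. Text against schedule.**

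| Item | Text | Table 2 |
|---|---|---|
| Baseline HBV DNA | Needed for eligibility (Exclusion criteria); status read at Visit 1 (HBV DNA monitoring) | Hepatitis row ticked at Visit 0, not at Visit 1 |
| Three-month test | Required | Hepatitis row not ticked at Visit 4 |
| Last-visit test | Required | Hepatitis row ticked at Visit 7 |
| Condition for the switch | ESSDAI non-response only | Visit 4 labelled as the switch checkpoint |

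**4. Exposure before the stop rule can act.**
- Monitoring section followed, sample drawn at Visit 4, baricitinib started the same day: exposure equals the laboratory turnaround. The documents do not give it; a matter of days is assumed here.
- Site works from Table 2 alone: the latest result is 12 - (-4) = 16 weeks old at the switch, and the next comes at week 24, after 24 - 12 = 12 weeks of baricitinib. This would depart from the monitoring section.

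**5. How many patients.** At the planned 30% control response, 70% of controls switch: 0.70 x 23 = 16.1 to 0.70 x 29 = 20.3, so about 16 to 20. Only the HBcAb-positive among them are concerned, and of those only the ones whose HBV DNA has turned detectable since screening. The documents give neither share.

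**The case against.** The strongest reply is that Table 2 contradicts nothing. Its hepatitis row is general screening for all participants, whereas HBV DNA monitoring is a conditional rule for a subgroup. The table is not exhaustive: it has no row for pregnancy testing, TSH or chest X-ray. The article condenses protocol Version 3.1, which is not shown and may hold the footnote and the steps for the switch. Other safeguards exist: liver function is tested at every visit, there are transaminase criteria for stopping, and a positive HBV DNA result already in hand would, on a sensible reading of the stop rule, bar baricitinib.

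Most of this stands. The monitoring section binds whatever Table 2 shows, and a missing footnote alone would not be worth raising. The wrong visit label has little consequence, because eligibility is governed by the exclusion criterion.

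What survives is the order of result and first dose. The article states the switch condition, and that condition is ESSDAI alone. A site that complies fully, drawing the sample at Visit 4, may still give baricitinib before the result returns. Liver tests do not fill the gap, because the protocol's own trigger is HBV DNA.

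**Conclusion.** The point holds as a minor safety-schedule matter. The required week-12 test is missing from the schedule, the baseline visit is mislabelled, and nothing makes the result a condition of starting baricitinib. For a compliant site the consequence is exposure for the length of the laboratory turnaround. The number of patients is unknown and probably small. The primary analysis is unaffected.

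Four stronger readings might be inferred, and the documents do not support them.
- *Table 2 cancels the three-monthly monitoring.* It does not; the text still requires the test.
- *The test falls at week 13, after the switch.* This takes three months to the day. Week 13 is within the Visit 4 window, and no separate off-visit date is set.
- *Switching controls would rely on a 16-week-old result and then take baricitinib unmonitored for 12 weeks.* That happens only where a site disregards the monitoring section.
- *Some 16 to 20 patients are at risk.* That is the expected number of all switchers, not of HBcAb-positive switchers with newly detectable DNA.

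The conclusion assumes that the three-month test is drawn at Visit 4 and that the full protocol adds no requirement at the switch beyond what the article states.

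**What to change.** - **Table 2:** add a row for HBV DNA in HBcAb-positive patients, ticked at Visit 0 (before randomisation), Visit 4 and Visit 7.
- **HBV DNA monitoring:** replace Visit 1 with screening (Visit 0) as the visit at which status is read. State that the three-month interval runs from the start of medication, so that Visits 4 and 7 satisfy it and the relabelling does not pull the first test forward to week 9. Leave the stop rule as it is.
- **Intervention description {11a}:** add a sentence such as: An HBcAb-positive control starts baricitinib only after an undetectable Visit 4 HBV DNA result.

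No test is added, since the baseline, three-month and last-visit tests are already required. The cost is a delay of some days (assumed, as turnaround is not stated) before these few controls switch, which slightly shortens their 12 weeks on baricitinib before the week-24 evaluation.

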#### Active TB monitoring

Patients with a history of active or latent TB who have documented evidence of appropriate treatment, have no history of re-exposure since their treatment was completed, have no clinical features of active TB, and have a screening chest X-ray with no evidence of active TB may be enrolled.

These patients will require TB activity monitoring every 3 months and at the patient’s last visit. If the patient had active TB during the study in the opinion of the investigator (according to the clinical features and chest X-ray or CT scan), he/she should be permanently discontinued from investigational product and should be referred to an infectious disease specialist immediately.

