### Adverse event reporting and harms {22}

An adverse event (AE) is any untoward medical occurrence (including an abnormal laboratory finding), in a patient or clinical trial subject administered a medicinal product temporally associated with the use of a study agent(s), whether or not related to the study agent(s), occurring as soon as the patient has signed the informed consent form and at any time during the study. All adverse events reported by the subject or observed by the investigators will be recorded in the CRF. AEs also include an undesirable medical condition occurring, even if no study treatment has been administered.

For all AEs, the investigator will assess the causal relationship between the study drug and the AE using his/her clinical expertise and judgment according to the following algorithm that best fits the circumstances of the AE:

The investigator will interpret and document whether or not an AE has a reasonable possibility of being related to study treatment, study device, or a study procedure, taking into account the disease, concomitant treatment or pathologies. The investigator will decide whether the patient will drop out of the study due to the AEs.

A “reasonable possibility” means that there is a cause and effect relationship between the investigational product, study device, and study procedure and the AE. The investigator answers yes/no when making this assessment.

A serious AE (SAE) is any AE from this study that results in one of the following outcomes: death; initial or prolonged inpatient hospitalization; a life-threatening experience (that is, immediate risk of dying); persistent or significant disability/incapacity; congenital anomaly/birth defect; important medical events that may not be immediately life-threatening or result in death or hospitalization but may jeopardize the patient or may require intervention to prevent one of the other outcomes listed in the definition above.

Record the incidence of AEs and SAEs, especially which may cause discontinuation of the study.

Attention should be paid to monitoring the risk of serious infections such as tuberculosis, hepatitis B and other infections after medication. The risk of thromboembolic events should be monitored. Other adverse events included abnormal blood routine test, abnormal liver and kidney function test, allergic reaction, and gastrointestinal reaction.

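### The 3-monthly TB monitoring rule covers only patients whose TB treatment is complete, although patients still on latent-TB treatment may enrol; the scope of the active-TB stopping sentence is unclear

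*Protocol article*

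**What the plan says.** The Exclusion criteria of the protocol article rule out active TB and inadequately treated latent TB, then allow exceptions. One admits a patient with latent TB who "completes at least 4 weeks of appropriate treatment prior to randomization and agrees to complete the remainder of treatment while in the trial". Two others admit patients with a history of active TB or of latent TB whose treatment is documented and finished.

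The section Active TB monitoring opens with "Patients with a history of active or latent TB who have documented evidence of appropriate treatment" and adds that they must "have no history of re-exposure since their treatment was completed". Its second paragraph begins "These patients will require TB activity monitoring every 3 months", with a further check at the last visit. The next sentence, "If the patient had active TB during the study in the opinion of the investigator", leads to permanent discontinuation of study drug and referral to a specialist.

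Four other places bear on the point:

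- Permanent discontinuation from investigational product has a list introduced by "In addition, patients will be discontinued from investigational product in the following circumstances". It names pregnancy, malignancy and venous thromboembolism.
- Table 2, under Participant timeline {13}, has a row "Infection screening like hepatitis and TB", ticked at screening and at week 24 only. Adverse events and concomitant medication are ticked at every visit.
- Adverse event reporting and harms {22} says, for all participants: "Attention should be paid to monitoring the risk of serious infections such as tuberculosis, hepatitis B and other infections after medication".
- Relevant concomitant care {11d} bars every medication other than study drugs, except to treat adverse events, and then permits low-dose glucocorticoids.

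**The concern.** The population in the monitoring section does not match the population that the entry criteria let in. A patient partway through latent-TB treatment at randomization is eligible, but cannot satisfy a description that presupposes completed treatment. As written, patients who have finished TB treatment get interval checks, and those whose latent infection is still being treated do not.

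The trial adds a JAK inhibitor in one arm, and in control-arm non-responders from week 12, and the harms section itself names TB as a risk to watch. Eight centres will apply this text. If it can be read in two ways, some sites may follow these patients as they follow the completed-treatment group and others may not. The same holds for whether active TB in such a patient invokes the mandatory stopping sentence or is left to individual judgement.

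**Working it through.** There is no figure to reproduce. The check is to follow each TB entry route through the rest of the article.

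**Step 1: who may enter.** There are three routes: (a) treated active TB, treatment finished; (b) treated latent TB, treatment finished; (c) latent TB with at least 4 weeks of treatment before randomization and the remainder during the trial.

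**Step 2: who is monitored.** The first paragraph of Active TB monitoring repeats the conditions of routes (a) and (b), including no re-exposure since completion. Route (c) is not mentioned, and its patients have no completion date from which re-exposure could be judged. The monitoring sentence refers back to the patients just described, so it reaches (a) and (b) only.

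**Step 3: who is covered by the active-TB sentence.** It speaks of the patient in the singular. Read with the sentence before it, it covers (a) and (b). Read alone under the section heading, it could cover anyone enrolled. The general discontinuation list does not settle this, because active TB is not on it.

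**Step 4: what route (c) patients do have.**

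| Provision | Routes (a), (b) | Route (c) |
|---|---|---|
| TB check every 3 months and at last visit | Yes | Not stated |
| Week-24 infection screen (Table 2) | Yes | Yes |
| Adverse-event review at each visit | Yes | Yes |
| General instruction to monitor TB risk | Yes | Yes |
| Active-TB stop-and-refer sentence | Yes | Ambiguous |

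**Step 5: the size of the gap in scheduled checks.** Follow-up is 24 weeks, with visits every 4 weeks. Three months is about 12 to 13 weeks, so the rule produces checks at about week 12 and at week 24: two checks. Route (c) has the week-24 screen only: one. The difference is 2 − 1 = 1 check, at about week 12.

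**Step 6: whom the missing check concerns.** A route (c) patient randomized to baricitinib has 24 weeks of exposure with no TB-specific check before the end. A switched control starts baricitinib at week 12 and reaches the week-24 screen after 24 − 12 = 12 weeks, so for that patient the missing check falls at the start of baricitinib. A control who stays on HCQ alone receives no baricitinib.

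**Step 7: a linked contradiction.** Route (c) requires TB treatment to continue in the trial. The concomitant-care section permits only study drugs, treatment for adverse events and limited glucocorticoids. Taken literally, the two cannot both be followed.

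**Comparison within the article.** For hepatitis B, the group admitted by exception (core-antibody positive, DNA negative) is the same group that the section HBV DNA monitoring covers. For TB, that link is made for two of the three routes, which suggests an oversight rather than a decision.

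**The case against.** The strongest reply is that these patients are followed. A reader might infer from the monitoring section that they have no TB monitoring at all and that sites have no trigger to act on reactivation. The documents do not support that: Table 2 gives every participant a week-24 screen, adverse events are reviewed at each visit, the harms section directs attention to TB without limiting it to a subgroup, and the investigator may withdraw a patient because of an adverse event. A reader might also infer that untreated latent TB can enter. It cannot: the exception requires at least 4 weeks of appropriate treatment.

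It can also be said that the active-TB sentence is naturally read to cover any patient. That reading is open, and so it would be wrong to state that these patients lack a stopping rule. The sentence nevertheless follows directly on one about a defined subgroup, and no general rule elsewhere removes the doubt.

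Finally, this is a journal article, and the full protocol may say more. That answers complaints about absent detail, such as what follows if TB treatment is stopped early, and no such complaint is made here. It does not answer the mismatch, because the article prints a dedicated section with its own population, interval and action, and that population disagrees with its own entry criteria.

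**Conclusion.** The point holds as a mismatch of scope. Patients enrolled on ongoing latent-TB treatment are left out of the 3-monthly monitoring as written, and whether the active-TB sentence applies to them is ambiguous. In scheduled checks the shortfall is one, at about week 12, and it matters most for patients randomized to baricitinib.

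This rests on reading the monitoring sentence as referring to the patients in the paragraph before it, and on taking 3 months as the visit nearest week 12. The documents give no number of patients expected by this route; it may be small or even zero. The primary endpoint and the sample size are unaffected. It should be corrected because it bears on patient safety and the change is cheap.

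**What to change.** Reconcile the TB exceptions in the Exclusion criteria, the section Active TB monitoring, the general discontinuation list and the TB row of Table 2, so that:

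1. the population named in Active TB monitoring matches the TB entry exceptions, or the protocol says explicitly that patients on ongoing latent-TB treatment are handled differently, and why;
2. the active-TB sentence states whether it applies to all enrolled patients or to a subgroup, and the discontinuation list agrees with it;
3. Table 2 shows the TB checks that the monitoring section requires;
4. the ban on other medication in Relevant concomitant care {11d} is squared with the requirement to complete TB treatment during the trial.

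The clinical rule in each case is for the sponsor to decide. The cost is a few sentences and a revised table row. If the monitored group is widened, the downside is about one additional TB activity check, at about week 12, for each patient entering by this route.
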